### Secondary outcome measures

Cultural competency of HCP while child hospitalized (parent report).Instructions for medical follow up given by clinician (parent report).Follow-up rates of children within 1-month (range 3–6 weeks) post hospitalization for ALRI (parent report).In children with chronic wet cough:Antibiotics prescribed at follow-up (parent report).Adherence to prescribed antibiotics (self-report).Cough resolution at 6–12 weeks post discharge (parent report).Discharge summary audit: An audit of the discharge summary to evaluate patient management (see Additional file 6):First Nations ethnicity recorded.Local clinic/doctor identified.Instructions given to parent to follow up in 1-month with local doctor.Instructions to the local clinic/GP clearly stipulates to check child for ongoing chronic wet cough, absence or presence of ongoing other signs and suggest appropriate management if chronic wet cough is present. Link to appropriate clinical practice guidelines for the management of chronic wet cough provided.*Note: an audit of discharge summaries will be conducted each month. De-identified results (audit and feedback) will be provided to the HCPs each month at their regular departmental meeting to facilitate service improvement as part of implementation process.*
Secondary outcome measures 1–4 will be captured by telephone follow-up at 6–12 weeks post discharge. To ensure culturally secure engagement, a standardized script will be used to provide context by the telephoning research officer. The research officer who telephones the parent will first introduce themself and identify from where they are calling. The officer will provide context for the call, i.e., remind parent about the study and child’s recruitment at recent hospital admission. The questions are outlined in question 2, 3, 5 of Additional file 7.

### Economic analysis

A stepped health economic evaluation will be undertaken to determine the cost-effectiveness of implementation and the economic cost-saving of cases with prevented bronchiectasis. Costs determined are: (i) Cost of provision of new service, including staffing, consumables, cost of training, electronic discharge system modifications; (ii) the extra cost of caring for a child with bronchiectasis over their lifetime for ~ 19% of children hospitalised with ALRI.

The economic evaluation aims to determine the cost of the implementation process, i.e., the cost of the medical follow-up strategy at a hospital and primary care clinic and to determine the cost-effectiveness of the program though evaluating the cost-saving from preventing bronchiectasis in children i.e., where a child who had chronic wet cough and received appropriate follow-up and management thereby resulting in resolution of the cough will be seen as a case of bronchiectasis prevented. Cost data for the economic evaluation will include all costs associated with implementation at the hospital and primary care clinic (i.e., the strategy cost) and will include costs such as training workshops, health organization changes in process or functions at both hospital and local primary care clinic, facilitation of staff behaviour change, including identification of champions, audit and feedback, identification of barriers and enablers, and ongoing engagement with facilitation of practice change. The cost of the implementation strategy will be based on the current implementation package at Perth Children’s Hospital (PCH), adapted for other participating hospitals. This is the best estimate based on data, thus far, to deliver this strategy at a hospital site.

The economic evaluation will present findings as a series of steps, first reporting the costs and outcomes of the strategy separately, then reporting a series of incremental cost-effectiveness ratios (ICERs) using a variety of key outcomes, including the number of children managed, and the estimated number of cases of bronchiectasis prevented.

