## Background

Respiratory illnesses account for 12% of the age-standardised mortality gap between First Nations and other Australians [1]. Respiratory disease is the second most common cause for hospitalisation among First Nations people [2]. First Nations children hospitalised with acute lower respiratory infections (ALRIs) are particularly vulnerable to developing bronchiectasis [3, 4], with 15–19% of First Nations children having bronchiectasis within 24-months post-hospitalisation with pneumonia or bronchiolitis [3, 4]. Children who present with persistent wet cough a month after hospitalisation are specifically at risk because they likely have protracted bacterial bronchitis which can progress to bronchiectasis [5]. If children are screened for persistent wet cough one-month post-hospitalisation and managed optimally if wet cough is still present, then bronchiectasis can potentially be prevented. Culturally secure assessment [6] and treatment [7–9] is important for optimal outcomes in First Nations contexts. That is, ensuring First Nations Australians receive care that acknowledges their unique cultural needs and differences.

The study protocol follows the Standard Protocol Items: Recommendations for Intervention Trials [10] (SPIRIT) and reporting will follow the Standards for Reporting Implementation Research (STaRI) [11]. The Consolidated Criteria for Reporting Qualitative research [12] (COREQ) will be used to report qualitative data findings.

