#### Pragmatic data collection

Ultimately, the studies power will depend on the ability to recruit participants from the limited (and difficult to estimate) pool of diagnosed patients within the study population. We estimate that within each of the three stages, somewhere between 50 to 150 eligible children will be recruited (based on an examination of historic data from the study sites). Of these, we expect ~ 20% to have chronic wet cough and meet the eligibility criteria to have their PC-QoL assessed. Thus, we aim to have data for 20 participants per combined regional sites per stage. Prior data, coupled with the above sample size calculation, determines the feasibility of the study.

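### The economic analysis counts each managed child whose wet cough resolves as one case of bronchiectasis prevented, which is an upper bound that favours the strategy

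*Protocol article*

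**What the plan says.** The Economic analysis section of the protocol article sets out how cases prevented will be counted. When a child with chronic wet cough is suitably followed up and treated, this "thereby resulting in resolution of the cough will be seen as a case of bronchiectasis prevented". The count then serves as one denominator in a series of incremental cost-effectiveness ratios, where it is called an estimate. The number of children managed is another. On the cost side the same section lists "the extra cost of caring for a child with bronchiectasis over their lifetime for ~ 19% of children hospitalised with ALRI".

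Elsewhere the protocol treats bronchiectasis as a possible outcome, not a certain one. The Background reports "15–19% of First Nations children having bronchiectasis within 24-months post-hospitalisation with pneumonia or bronchiolitis", a figure for all hospitalised children. Children with persistent wet cough a month after hospitalisation are described as "specifically at risk because they likely have protracted bacterial bronchitis which can progress to bronchiectasis", with no percentage attached. The Discussion says that good management can often, not always, prevent the disease.

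Under Pragmatic data collection, "somewhere between 50 to 150 eligible children will be recruited" in each stage. The next sentence reads "Of these, we expect ~ 20% to have chronic wet cough". The target is 20 children with PC-QoL data per stage. Cough resolution is a parent-reported secondary outcome at 6–12 weeks after discharge.

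**The concern.** The rule replaces two uncertain quantities with certainty.

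- **Progression.** Each child counted is given a probability of 1 of developing bronchiectasis without management. The Background says only that the underlying condition can progress.
- **Attribution.** Each resolution in a managed child is credited to the management. Some of these coughs would have cleared without it. A control child who was not managed and whose cough cleared scores zero, so subtracting the control stage does not take spontaneous resolution out.

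Both act in the same direction, towards more cases prevented, a larger saving and a lower cost per case. The outcome counted is also a short-term parent report standing in for a disease that the Background measures over 24 months.

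Health economics is one of the protocol's specific objectives, and the saving from prevented bronchiectasis is a stated purpose of the evaluation. The rule is written into the plan, so this is not a detail left to a later document.

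**Working it through.** The protocol gives no number of cases prevented and no saving, so there is no stated figure to reproduce. The check asks what the protocol's own inputs imply for the one-for-one rule.

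**Inputs.** R = 15–19%, bronchiectasis within 24 months among all hospitalised children (Background). w = 20%, share with chronic wet cough (Pragmatic data collection). N = 50–150 recruited per stage (same section). RR, the relative risk of bronchiectasis with versus without persistent wet cough, is not given and is varied.

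**Step 1: numbers.** Wet-cough children per stage = N × w = 50 × 0.20 to 150 × 0.20 = 10 to 30, and 20 at N = 100, which matches the target of 20. Per 100 hospitalised children, 15–19 cases of bronchiectasis are expected against about 20 children with wet cough. If more than 15/20 = 75% (R = 15%) or 19/20 = 95% (R = 19%) of those 20 were managed and resolved, the rule would count more cases prevented than are expected to occur.

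**Step 2: risk in wet-cough children.** From R = w·p_w + (1 − w)·p_0 and p_w = RR·p_0,

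p_w = R·RR / (w·RR + 1 − w).

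If a resolved cough removes the child's whole risk, the overcount from the one-for-one step is 1/p_w.

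| RR | p_w, R = 15% | Overcount | p_w, R = 19% | Overcount | Cases per 20 resolved coughs |
|---|---|---|---|---|---|
| 1 (no enrichment) | 0.150 | 6.67 | 0.190 | 5.26 | 3.0–3.8 |
| 3 | 0.321 | 3.11 | 0.407 | 2.46 | 6.4–8.1 |
| 5 | 0.417 | 2.40 | 0.528 | 1.89 | 8.3–10.6 |
| 10 | 0.536 | 1.87 | 0.679 | 1.47 | 10.7–13.6 |
| all cases in wet-cough group | 0.750 | 1.33 | 0.950 | 1.05 | 15–19 |

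The rule would give 20 in every row. The factor reaches 3 only if RR is at most about 3.2 (R = 15%) or 2.2 (R = 19%).

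**Step 3: does differencing the stages remove spontaneous resolution?** All rates here are assumed, because the protocol gives none. Take 20 wet-cough children per stage, 20% managed in the nil stage and 80% post, with resolution in 80% if managed and 40% if not.

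- Rule: post 20 × 0.80 × 0.80 = 12.8; nil 20 × 0.20 × 0.80 = 3.2; difference 9.6.
- Proportion resolved, all children: post 0.80 × 0.80 + 0.20 × 0.40 = 0.72; nil 0.20 × 0.80 + 0.80 × 0.40 = 0.48. Additional resolutions: 20 × 0.24 = 4.8.

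The differenced rule is still 9.6/4.8 = 2.0 times too high, before any progression risk. In general the factor is r_m/(r_m − r_u), where r_m and r_u are resolution with and without management. With r_m = 80% it is 1.33 at r_u = 20%, 2.0 at 40% and 4.0 at 60%.

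**The case against.** **The plan already takes increments and calls the count an estimate.** Incremental ratios imply a comparator, and secondary outcomes are compared across all three stages. This has some force, since the text does not say that control resolution will be ignored. But under the rule as worded only managed children can score, so Step 3 applies after differencing. The word *thereby* might be meant to restrict the count to coughs that cleared because of management. A parent report of resolution cannot identify those children one by one; only a comparison of proportions can.

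**The excess may be small.** This stands. A reader might infer that cases averted are overstated several-fold. That follows only if the 15–19% risk for all hospitalised children is carried over to wet-cough children, whom the protocol singles out as at higher risk, or if resolution rates are assumed. The protocol's figures also allow an excess of only 5–33%.

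**Other results are unaffected.** This stands too. A reader might infer that none of the planned ratios can be interpreted. Costs and outcomes are to be reported separately first, and the ratio per child managed does not use the rule.

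**The cost side may already scale the saving.** This is possible. The section does not say how the 19% item combines with the count, so a contradiction between the two cannot be shown, only a link left unstated. Using 19% instead of 15% changes that input by a factor of 19/15 = 1.27 at most.

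**Conclusion.** The point holds as a matter of direction: the rule gives an upper bound on cases prevented, and it conflicts with the protocol's own account of progression. The one-for-one step alone overstates cases averted by about 1.05 to 6.7 times. That range assumes that w is about 20%, that 15–19% is the risk without the strategy, and that a resolved cough removes the child's whole risk. If resolution removes only part of it, the excess is larger. The 6.7 end corresponds to wet cough carrying no extra risk, which the Background contradicts. The 1.05 end requires every case to arise in the wet-cough group. Both are bounds, not estimates. Excess from spontaneous resolution comes on top, but the protocol gives no rates from which to size it. The effect on the saving is less certain still, because the use of the 19% is not explained.

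The 75–95% figure is risk given chronic wet cough. It must not be reused as risk given cough still unresolved at 6–12 weeks, a smaller group. With an assumed 40% resolving, 20 × 0.60 = 12 of 100 hospitalised children would remain unresolved, and 15–19 cases among 12 children would need a risk of 125–158%.

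This is a secondary economic output. The primary PC-QoL comparison and the sample size do not depend on it.

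**What to change.** Replace the counting rule in the Economic analysis section with:

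cases prevented = (number of children with chronic wet cough) × (post minus nil difference in the proportion with cough resolved at 6–12 weeks, whether or not managed) × (probability of bronchiectasis averted per additional resolved cough).

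- State that probability with its source, keep it below 1, and vary it over a wide range in a sensitivity analysis. Carry the uncertainty of the resolution difference through as well, since about 20 children per stage will give a wide interval.
- If the one-for-one count is kept, label it an upper bound.
- On the cost side use the full 15–19%, and state how it combines with the count so that risk is applied once and on one denominator.
- Report ratios on observed outcomes (per child managed, per additional cough resolved) alongside. They do not depend on the progression assumption.

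The cost is revised wording, a small amount of modelling and a probably less favourable saving. No new data are needed, because cough resolution is already a secondary outcome. The article states that recruitment has not begun, so the rule can be changed before any result is known.

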### Implementation outcomes

The following implementation outcomes will be measured to evaluate implementation success for the strategy [24]:Fidelity to core components of the strategy will be assessed as per Table 1 outcomes.Acceptability (“the perception among implementation stakeholders that the strategy is agreeable… and satisfactory” [24]) will be assessed for HCPs and parents through semi-structured interviews (see Additional file 1, Additional file 2, Additional file 3, Additional file 4, Additional file 5).Appropriateness (“the perceived fit of the strategy for the given practice setting” [24]) will be assessed with the 22-item TCU Workshop Evaluation (WEVAL) form to assess the perceptions of the strategy directly after implementation (http://ibr.tcu.edu/wp-content/uploads/2013/06/weval.pdf) and the 14-item TCU Workshop Assessment Follow-Up (WAFU) to assess changes 6-months after (http://ibr.tcu.edu/wp-content/uploads/2013/06/wafu.pdf).Implementation cost will be addressed as described under the economic analysis section.Penetration and adoption will be assessed as (i) the number of HCPs who participated in training out of the total number of HCPs, and (ii) audit of discharge summaries as described in secondary outcome measures.Sustainability will be addressed through focus groups and interviews with HCPs and parents in the final months of the project and feedback questionnaires for HCPs.
We acknowledge that given the study is being conducted in First Nations settings, evaluation of implementation outcomes must consider the diversity within First Nations contexts [25]. Therefore, assessment of “acceptability” and “appropriateness” will include identification of First Nations leadership, governance, co-design, partnership and involvement in implementation processes.

### Study and participant timeline

The timeline for the study is outlined in Table 2.

**Table 2 Tab2:**
[figure not shown]
Timeline of study for ALL sites*

Timing of Q1 at each site/cluster will vary. The table above is a conceptual map showing the chronology only. Time intervals between different stages will vary due to local site-related logistics

*Q* quarter

^*^The above timeline applies to individual study sites/clusters

### Sample size

The primary outcome measure for this trial is the PC-QOL (8-item version). There is limited data available to inform a robust sample size calculation and it is acknowledged that there are challenges with estimating potential cohort sizes within the limited remote communities included in this study, thus a pragmatic approach has been taken to the sample size calculations. Data (unpublished) from our previous studies using the PC-QOL suggests a conservative standard deviation of 1.3, a historic mean score of approximately 2.7, a pre-implementation mean score of approximately 3.6, and a post-implementation mean score of approximately 4.3. Two calculations were carried out, one based on a two-sided T-Test (to reflect an examination of the intervention effect within a single site), and the other based on the overall analysis (reflecting the clustered, within site, nature of the data).

Single site analysis with at least 12 participants with chronic wet cough in each period will have > 80% power to detect a nil-intervention (2.7) v post-intervention (4.3) difference of 1.6, alpha 0.05. Full sample (clustered) analysis with at least 5 participants per cluster (4) per period (assuming COV 0.65, ICC 0.01) will have > 95% power to detect a nil-intervention (2.7) v post-intervention (4.3) difference of 1.6, alpha 0.05; at least 10 participants per cluster (4) per period will be required to have > 80% power to detect a difference of 0.9 (alpha 0.05). Adjustments for multiple comparisons were not made as calculations are to provide guidance only, with final sample size being dependent on cohort sizes and diagnosis counts during observation periods; sample size calculations were carried out using PASS [26].

#### Pragmatic data collection

Ultimately, the studies power will depend on the ability to recruit participants from the limited (and difficult to estimate) pool of diagnosed patients within the study population. We estimate that within each of the three stages, somewhere between 50 to 150 eligible children will be recruited (based on an examination of historic data from the study sites). Of these, we expect ~ 20% to have chronic wet cough and meet the eligibility criteria to have their PC-QoL assessed. Thus, we aim to have data for 20 participants per combined regional sites per stage. Prior data, coupled with the above sample size calculation, determines the feasibility of the study.

### Recruitment

#### Recruitment of Nil-intervention control group

A researcher will access hospital records of patients who have been previously (within the last 6-months) hospitalised at the hospital site with ALRIs. A recruitment letter will be sent to the parent from the hospital containing an overview of the study and opt-out instructions. If an opt-out response was not received within 3 weeks of posting the letter, a clinician researcher will contact the parent via telephone. The parent will be given the opportunity to consent via telephone. The questions will be administered via telephone.

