### Who will take informed consent?

A trained research officer will contact potential participants/parents and undertake the informed consent process. This person will use culturally secure patient information documents that have undergone a rigorous development process that included feedback from stakeholders and 18 Western Australian First Nations community members from regional, remote and metropolitan areas.

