### Health outcome/primary outcome measure (Quality of Life (PC-QoL))

The primary outcome is the parent-proxy Cough-specific Quality of Life (PC-QoL) for children with chronic wet cough. Effective follow-up and management of children hospitalized with ALRIs will be assessed by measuring PC-QoL between 6 weeks and 3 months after hospitalization. We will use the 8-item version of the PC-QOL tool that has been shown to be a valid, reliable, and responsive tool for measuring the burden of chronic cough in children. This tool has been used effectively in First Nations settings [17, 18].

Rationale: children with ongoing respiratory symptoms and cough post hospitalization will have improved quality of life if they receive effective medical follow-up at one-month post discharge. The PC-QoL scores will be compared pre and post implementation in different children who had a chronic wet cough post-discharge. Children with chronic wet cough post-hospitalization who received timely follow-up and optimal management will have better cough specific QoL than children who did not. It has been determined, using the anchor method, that 0.9 is the calculated minimum important difference in PC-QOL [23].

Respiratory symptoms after ALRI should typically resolve within 4 weeks. Children with ongoing wet cough 4 weeks post-hospitalization are likely to have protracted bacterial bronchitis that should resolve if detected and managed in a timely way. Hence, if children receive appropriate follow-up and management a month after discharge then we expect their cough related QoL to be better after 6–12 weeks than those who did not (waiting 6–12 weeks allows time for management to be completed in those children with chronic wet cough who may require up to a month of antibiotic treatment).

The PC-QoL tool will be administered by a research officer in-person at the hospital sites, over the phone, or electronically (online option via REDCap for those participants who would prefer this option). Participants will be contacted by the research officer via text message or telephone.

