#### Recruitment of participants on hospital wards

**In General:**

Health-information control group and post-intervention group:Identified through hospital electronic record systems or equivalent to identify if a First Nations child has been admitted with an ALRI.A researcher will invite the parent, while on the ward ***during the child’s admission***, to participate in the study using the following process:Lung health information will be given to parents in a culturally secure way, which includes the use of an information flip chart [27].The study will be explained verbally and via written study information.Parents will be invited to participate in the study (with follow-up) and to consent or opt out of an interview.If consenting, an interview will be conducted.A First Nations researcher will be available for all interactions with First Nations participants.During recruitment, parents will be asked for the best contact number for a follow-up phone call to obtain follow-up data from parents.

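### The protocol contradicts itself on who telephones nil-intervention parents and does not say who questions them, so interviewer role could become aligned with the primary contrast

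*Protocol article*

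**What the plan says.** The protocol article describes contact and questioning of parents in several places.

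- **Recruitment of Nil-intervention control group.** After the opt-out letter and a three-week wait, "a clinician researcher will contact the parent via telephone". The parent may then consent by telephone, and "The questions will be administered via telephone". The last sentence is passive and names no role.
- **Who will take informed consent?** As a general rule, "A trained research officer will contact potential participants/parents and undertake the informed consent process".
- **Health outcome/primary outcome measure.** "The PC-QoL tool will be administered by a research officer in-person at the hospital sites, over the phone, or electronically", and "Participants will be contacted by the research officer via text message or telephone". Neither sentence distinguishes between stages.
- **Secondary outcome measures.** Outcomes 1 to 4 come from a telephone call at 6 to 12 weeks: "The research officer who telephones the parent will first introduce themself and identify from where they are calling". A standardised script gives context and reminds the parent that the child was recruited during the recent stay.
- **Recruitment of participants on hospital wards**, covering the two later groups. "A First Nations researcher will be available for all interactions with First Nations participants".
- **Plans for assessment and collection of outcomes.** Each site's team is a First Nations research officer and a clinician researcher.
- **Data management.** Each site's team is an Aboriginal research officer and a second research officer.

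The value of interest is the nil-intervention versus post-intervention difference in PC-QoL (Statistical methods for primary and secondary outcomes). Blinding is marked not applicable.

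**The concern.** PC-QoL and secondary outcomes 1 to 4 are reported by parents who know their circumstances, and nobody is blinded. They include items on which the interviewer's identity could plausibly affect the answer: how culturally competent the hospital's health care providers were, whether the child was taken back for follow-up, and whether prescribed antibiotics were taken. A parent may answer a clinician differently from a research officer.

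If a clinician questions the nil-intervention parents and a research officer questions the post-intervention parents, any such difference enters the estimated program effect. Role would then be constant within the nil stage and different in the post stage, so it would coincide with the two-level stage term. Site, calendar week, sex and age, the other terms listed for the primary model, could not separate the two.

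The issue is who asks. The mode of contact is a separate matter, although it is convenient to record both.

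**Working it through.** **Step 1: the sections side by side.**

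| Task | Nil-group section | Other sections |
|---|---|---|
| First contact | Clinician researcher | Research officer (consent section, primary outcome section) |
| Consent | By telephone; role not named | Research officer (consent section) |
| PC-QoL | By telephone; role not named | Research officer, no stage named; online completion also allowed |
| Secondary outcomes 1 to 4 | By telephone; role not named | Research officer, no stage named |
| Second member of site team | Not addressed | Clinician researcher in one section, second research officer in another |

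The first row is a direct contradiction and needs no inference. The next three rows are gaps in the nil-group section. Three consecutive sentences there cover the call, the consent and the questions, with one actor and no second call mentioned, so the natural reading is that the clinician researcher does all three. The general sections point the other way. The last row is a second contradiction.

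**Step 2: does the script fit?** The reminder presupposes recruitment on the ward. Nil-group families are recruited after discharge, by letter and telephone, so the script as described cannot be read to them unchanged.

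**Step 3: the plan's own figure.** No stated figure is in dispute. To confirm the inputs (SD 1.3, two-sided alpha 0.05, from Sample size), take the single-site calculation with 12 per period and a difference of 1.6. The standard error is 1.3 × √(2/12) = 0.531, the noncentrality 1.6/0.531 = 3.01 on 22 degrees of freedom, and the power 82.1%. The plan states more than 80%, so the figure reproduces.

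**Step 4: illustration of sensitivity.** The documents give no size for an interviewer effect, so a shift b is assumed, with no true program effect and an unadjusted two-sided t-test. The noncentrality is b / (1.3 × √(2/n)). The standard error is 0.411 for n = 20 per stage (the aim under Pragmatic data collection) and 0.291 for n = 40 (four clusters of 10, from Sample size).

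| Assumed shift b (points) | Noncentrality, n = 20 | Rejection, n = 20 | Rejection, n = 40 |
|---|---|---|---|
| 0.2 | 0.49 | 7.6% | 10.4% |
| 0.3 | 0.73 | 11.0% | 17.5% |
| 0.5 | 1.22 | 22.0% | 39.7% |
| 0.9 (the minimum important difference) | 2.19 | 56.9% | 86.4% |

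The table shows what a bias of each size would do. It is not evidence that one exists.

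**The case against.** A reader might infer that the plan has clinicians question the nil-intervention parents and research officers question everyone else. The documents do not support that as a settled fact.

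- The nil-group section names the clinician researcher only for contact.
- The only explicit rule on who administers the primary outcome names a research officer and does not limit this to later stages. The same holds for the secondary outcome call.
- Job titles are used loosely. The clinician researcher in one section and the second research officer in another may be the same post.
- The script is said to give context, not to standardise the outcome questions. Those are in an additional file that is not shown, and a nil-group version may exist.
- A First Nations research officer is on every site's data collection team, so absence from nil-group calls is not shown, although the explicit assurance for study contacts appears under ward recruitment.
- PC-QoL may be completed online, in which case no interviewer is involved.
- No direction can be argued. More favourable answers to a clinician would raise nil-group scores and understate the program effect; more candid answers could do the opposite.

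All of this stands, and it limits the point to a contradiction and an omission. It does not remove the point. A site that follows the section written for the nil group could use a clinician, while one that follows the general sections would not, and nothing in the text prevents role from lining up with stage.

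**Conclusion.** The protocol contradicts itself on who contacts nil-intervention parents and on who the second data collector is, and it leaves open who questions the nil group. The script described does not suit that group. Alignment of interviewer role with the primary contrast is the natural reading of the nil-group section, but not the only reading of the whole protocol.

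If it occurred, the planned model could not separate it from the program effect. How large the resulting bias would be, and which way it would run, cannot be said from the documents. The rejection rates above rest on assumed shifts and an unadjusted test, and should be read only as showing that modest shifts matter at these sample sizes. The secondary items on cultural competency, follow-up and adherence are where an effect of the questioner is most plausible.

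The text should be reconciled before recruitment, which had not begun according to Trial status. Nil-stage interviews could not be repeated later under matched conditions.

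**What to change.** 1. Reconcile the sections on consent, primary outcome, secondary outcomes, nil-group recruitment, outcome collection and data management, so that one role, the trained research officer with a First Nations researcher available, administers PC-QoL and the secondary questions in all three stages.
2. In the nil-group section, limit the clinician researcher to screening records and sending the letter or, at most, to first contact, and name who takes consent and asks the questions.
3. Use one script for all stages, with an opening line for nil-group families that does not refer to recruitment on the ward.
4. Record interviewer role and mode for every questionnaire in REDCap. If any clinician-administered questionnaires occur, report a sensitivity analysis restricted to those given by a research officer. This is informative only if the nil stage contains enough of them, so recording does not replace item 1.

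The cost is protocol and script wording and two database fields. Research officers are already planned at each site. The downside is some rescheduling of nil-group calls.
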